### Safety

We will report treatment induced SAEs within 15 days following notification through a government based internet portal to the accredited institutional review board that approved the protocol. Treatment induced SAEs that result in death or are life threatening will be reported within seven days.

### Sample size considerations

Based on the most recent meta-analysis, we expect a pain response in 60% of patients following standard radiotherapy [3]. Pain response after stereotactic radiotherapy is assumed to be 85% [8, 9]. We expect that approximately 90% of patients who are offered SBRT treatment, will accept the offer. Cross-over from control arm to the SBRT treatment arm is extremely unlikely, since only patients who are randomly selected to receive SBRT are informed about the treatment. Taking a one-sided α of 5% and a power of 80%, we require 49 patients per treatment arm to show a statistically significant difference of 15% in pain response. The reason to choose a one sided α is that, although improbable, inferior pain response after stereotactic treatment would lead to the same action as no difference at all between the two treatment regimen. This is because the SBRT treatment will only be implemented if it is significantly better than the usual care, since SBRT treatment is more complex, less convenient for patients, and more expensive than standard radiotherapy. Finally, to allow for a 10% drop out rate, recruitment of 55 patients per group is intended. We expect to complete recruitment within 18 months based on the number of patients we treat in our center annually.

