### Random selection

Eligible patients are randomly selected from the sub cohort on a 1:1 basis with varying block sizes (*n* = six or eight) using an in-house randomization computer program. The radiation oncologist will offer the experimental intervention (i.e. SBRT) to the randomly selected patients. If they accept the treatment offer, they will sign informed consent for participation in the VERTICAL study. Patients who refuse the SBRT will receive care as usual (i.e. standard radiotherapy). According to the cmRCT design, patients in the sub cohort who are not randomly selected will not be informed about the experimental intervention, nor will they be informed about their participation in the control arm of the VERTICAL study. Outcomes in randomly selected patients are compared with the outcomes in eligible patients not randomly selected who received standard radiotherapy (Fig. 1).

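### The sample size paragraph claims 80% power for a 15% difference, but under its stated one-sided 5% level 49 per arm matches 22.5 points; power for 15 points (60% vs 75%) is about 48%

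*Protocol article*

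**What the plan says.** All the design inputs stand in the Protocol article, mostly under Sample size considerations:

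- Control arm: "we expect a pain response in 60% of patients following standard radiotherapy".
- Experimental treatment: "Pain response after stereotactic radiotherapy is assumed to be 85" per cent.
- Uptake: "We expect that approximately 90% of patients who are offered SBRT treatment, will accept the offer".
- Contamination: "Cross-over from control arm to the SBRT treatment arm is extremely unlikely".
- Error rates: "Taking a one-sided α of 5% and a power of 80" per cent.
- Result: "we require 49 patients per treatment arm to show a statistically significant difference of 15% in pain response", raised to 55 per group for 10% dropout.

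Under Random selection, allocation is 1:1 and patients who decline SBRT get standard radiotherapy. Under Data analysis, the primary comparison is by intention to treat with a χ² test on the proportion responding.

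**The concern.** The paragraph assumes response rates 25 points apart and then names a 15-point difference as what the sample size will show with 80% power. Allowing for refusals brings 25 points down to 22.5, not 15. No other section sets a 15-point target.

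The detectable difference is the figure readers use to interpret a non-significant result. The same paragraph says that SBRT will be implemented only if it is significantly better, so a non-significant result has a practical consequence. If the sentence is taken at its word, such a result would suggest that a 15-point benefit had been tested with good power and not found.

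**Working it through.** **Inputs.** p1 = 0.60, SBRT response 0.85, acceptance 0.90, no control cross-over, one-sided α = 0.05 (z = 1.645), power 0.80 (z = 0.842), 1:1 allocation. One assumption is added: refusers, who receive standard radiotherapy, respond at 60%.

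**Step 1: the intention-to-treat contrast.**

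p2 = 0.9 × 0.85 + 0.1 × 0.60 = 0.765 + 0.060 = 0.825, so the difference is 0.825 − 0.600 = 0.225.

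**Step 2: reproduce the 49.** The pooled-variance formula without continuity correction is

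n = [z_α √(2 p̄ q̄) + z_β √(p1 q1 + p2 q2)]² / (p2 − p1)²

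Here p̄ = 0.7125 and q̄ = 0.2875. Then 2 p̄ q̄ = 0.4097 (root 0.6401), and p1 q1 + p2 q2 = 0.2400 + 0.1444 = 0.3844 (root 0.6200).

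n = (1.645 × 0.6401 + 0.842 × 0.6200)² / 0.225² = 1.5746² / 0.050625 = 48.98, so **49 per arm**.

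Dropout: 49 / 0.9 = 54.4, so **55 per arm**. Both figures match the article.

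**Step 3: the same formula for other contrasts (one-sided 5%).**

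| Contrast | Difference | n per arm for 80% power | Power at 49 per arm |
|---|---|---|---|
| 60% vs 82.5% | 22.5 points | 49 | 80.0% |
| 60% vs 85% | 25 points | 39 | 88.0% |
| 60% vs 75% | 15 points | 120 | 47.6% |
| 70% vs 85% | 15 points | 95 | 55.4% |

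For a 15-point difference with control rates from 50% to 80%, the required n falls from 134 to 60 and never reaches 49.

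**Step 4: power for 15 points.** For 60% vs 75%, p̄ = 0.675, √(2 p̄ q̄) = 0.6624 and √(p1 q1 + p2 q2) = 0.6538.

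Power = Φ[(0.15 √n − 1.645 × 0.6624) / 0.6538]

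- n = 49: Φ[(1.0500 − 1.0895) / 0.6538] = Φ(−0.060) = 47.6%. Exact binomial enumeration of the uncorrected test gives 48.7%.
- n = 55, all evaluable: Φ[(1.1124 − 1.0895) / 0.6538] = Φ(0.035) = 51.4% (exact 51.9%).

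For 80% power, n = 119.5, so 120 evaluable per arm, or 120 / 0.9 = 133.3, so 134 recruited.

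**Step 5: a place where 15 points does appear.** The smallest observed difference that reaches one-sided P = 0.05 with 49 per arm, at a pooled rate of 0.7125, is 1.645 × √(0.4097 / 49) = 0.150.

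**The case against.** The strongest defence is that 15% is a correct number with the wrong label. As step 5 shows, it is almost exactly the smallest observed difference that would be significant with 49 per arm, and the sentence does speak of showing a significant difference. But the sentence opens with 80% power, and a true effect equal to the critical difference has power of only about one half. If the critical value was meant, the wording still needs correcting. The document does not show what was intended.

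Second, 49 can be reached another way: 60% versus 85% at a two-sided 5% level gives 48.9. The diluted contrast as the source of the 49 is therefore an inference. The two-sided route contradicts the one-sided level that the paragraph states and defends, and its difference is 25 points, so it does not support 15 either.

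Third, nothing operational depends on the 15%. No test, stopping rule or success criterion uses it, and the other figures agree with each other. That is true, and it is why the patient numbers need not change. The stated sensitivity is still wrong.

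Fourth, Data analysis counts dropouts as non-responders, so recruiting 55 is not equivalent to having 49 evaluable patients. With 10% dropout in each arm (assumed equal), the rates become 0.9 × 60 = 54% and 0.9 × 82.5 = 74.25%, and power at 55 per arm is about 72%. This is a separate matter. It does not affect the 22.5-point correction, but the corrected sentence should say that it refers to evaluable patients.

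**Conclusion.** The concern holds. Under the article's own inputs and its one-sided 5% level, 49 evaluable patients per arm give 80% power for 22.5 points (60% versus 82.5%), not for 15. At a true 60% versus 75%, power is about 48% with 49 per arm and 51% with 55, and 80% power would take about 120 per arm, some 2.4 times as many.

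These figures rest on the 60% control rate, a 60% response among refusers and a χ² test without continuity correction. The exact power for 15 points depends on the control rate: with 49 per arm it runs from 44% at a control rate of 50% to 73% at 80%. It does not reach 80% anywhere in that range.

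**What to change.** In Sample size considerations, replace the 15% with the difference that the calculation supports, for example: *49 evaluable patients per arm give 80% power (one-sided 5%) for an intention-to-treat difference of 22.5 percentage points, 60% versus 82.5%, that is, 25 points diluted by 90% acceptance.* Add that power for a true difference of 15 points (60% versus 75%) is about 50%, so a non-significant result does not exclude a benefit of that size.

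If the authors did mean the smallest observed difference that would be significant, they should label it so and keep it apart from the power statement.

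The cost is a correction of one sentence plus one added sentence. Sample size, significance level and recruitment stay as they are. The stated sensitivity becomes less favourable. Were 15 points really the target, the sample size itself would have to be reconsidered.

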### Data analysis

Data will be analyzed according to the intention to treat principle. Data of eligible patients who were randomly offered stereotactic radiotherapy will be compared with eligible patients who were not randomly selected and received standard radiotherapy. In case of dropout (i.e. patients not surviving longer than three months or patients unable to provide pain scores and analgesic use), a worst-case analysis will be performed: dropped-out patients will be classified as non-responders. In case of substantial refusal of the SBRT offer in the intervention arm, instrumental variable analysis will be used to account for non-compliance [26]. The primary outcome (i.e. proportion of patients with response to radiotherapy) will be presented in absolute numbers and proportions. Differences in pain response will be compared by χ2 test. If randomization fails, imbalances between baseline characteristics will be adjusted by logistic regression analysis. Differences in duration of response and overall survival will be analysed by Kaplan-Meier analysis and log rank test. Toxicity will be presented as the overall incidence of grade 3–4 toxicity and incidence of vertebral compression fractures. Differences will be tested with the χ2 test. A comparison in QOL will be made between the baseline QOL and at predefined intervals after treatment. A change of 10% of the scale breadth will be considered a clinically relevant change of QOL [27]. Data will be presented as improved (≥10% increase), stable, or worsened (≥10% decrease) QOL. We will evaluate the pattern of QOL as a continuous outcome over time using mixed models. Differences with a *P*-value <0.05 will be considered statistically significant. We have planned to perform an interim analysis after inclusion of half of the patients (i.e. 55 patients) when they have completed their follow up (i.e. three months pain assessment).

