To our knowledge, six other randomized studies on spinal SBRT are currently being conducted (Table 3) [36–41]. Only two other trials require both CT and MRI imaging for the delineation of the spinal metastases [37, 38], however, these trials delineate the whole bony compartment (i.e. the CTV) that contains the metastasis instead of using an simultaneous integrated boost approach. They also have strict instructions on how to apply the standard and stereotactic body radiotherapy in contrast to our more pragmatic approach, offering radiation oncologists leeway in fractionation schedule. Furthermore, the VERTICAL trial distinguishes itself from these trials by applying the cmRCT design. The cmRCT design was proposed as a variant of classic pragmatic randomized controlled trials (RCTs) and addresses some common difficulties associated with those RCTs, such as disappointment bias, drop-outs, slow recruitment, and poor generalizability [13]. Patients and doctors often have a strong preference for the experimental treatment that has not proven to, but is expected to be superior. Investigators of the RTOG 0631 trial indeed experience that patients and their physicians prefer the SBRT treatment over standard radiotherapy [[name], personal communication]. Consequently, patients allocated to the standard arm may show disappointment when reporting outcomes. This is of particular concern since the primary endpoint consists of a subjective outcome (i.e. pain scores). By using the cmRCT design however, control patients are unaware of being allocated to the control arm, which will prevent disappointment bias in observed outcomes. Furthermore, standard of care is likely to be unaffected by treatment allocation and will therefore better resemble routine practice. We also expect lower drop-outs rates since patients in the control arm are not likely to withdraw from standard care, which may be of particular interest in this fragile patient population. Because of this fragility, researchers in this field should make an effort to optimize recruitment rates. The use of the cmRCT design may foster recruitment rates by its unique informed consent procedure. A reason not to take part in classic randomized studies might be that patients cannot be guaranteed to receive the desired experimental treatment. Furthermore, once participating, patients are often allowed to participate in one trial at a time only. By contrast, patients participating in a cmRCT study give broad informed consent to participate in randomized trials, but not to specific trials which may increase recruitment rates. Moreover, the cmRCT cohort offers an infrastructure which allows the conduct of randomized trials simultaneously. Finally, recruitment in cohort studies is usually more manageable compared with recruitment in RCTs. The inclusion rates in the PRESENT cohort for example are promising: the participation rate is 83%, and 88% of the participating patients have given informed consent for broad randomization to experimental interventions. The use of a cohort in cmRCT studies offers more potential advantages. Palliative patients willing to participate in randomized trials often represent a relatively healthier and higher-educated subgroup. By using a cohort as a recruitment pool for RCTs, a more routine population is included since recruitment for cohort studies is generally less selective. Moreover, the cohort provides information on baseline characteristics and outcome measurements (i.e. the regular cohort measures) of drop-outs, which is essential in the data analysis. Patients allocated to the control arm, are cohort participants who receive the current standard of care (i.e. standard radiotherapy in the PRESENT case). In our department, the standard of care for patients with bone metastases will change from standard radiotherapy to automatically generated conformal treatment plans. Would the VERTICAL trial have been conventionally conducted, this could have been problematic since control patients in the VERTICAL trial would then have been withhold from standard of care. However, the cmRCT design has the advantage that experimental interventions are compared with the most up-to-date standard of care, instead of competing with outdated treatments, which is often the case in completed classic RCTs. Finally, a valuable feature of the cmRCT design is the opportunity to evaluate and quantify the acceptance rates of the offered treatment (i.e. SBRT). This offers new insights into patient preferences and reasons for refusal of SBRT. We feel that prevention of disappointment bias, more efficient and less selective patient recruitment, up-to-date standard of care, and quantifying patients’ preference could significantly improve trials conducted according to the cmRCT design.

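### The dropout inflation to 55 per arm assumes that dropouts leave the analysis, but the analysis counts them as non-responders; power is about 72%, not the stated 80%

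*Protocol article*

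**What the plan says.** In the protocol article, Sample size considerations gives the planning inputs. For control, "we expect a pain response in 60% of patients following standard radiotherapy". For the experimental treatment, "Pain response after stereotactic radiotherapy is assumed to be 85" per cent. On uptake, "We expect that approximately 90% of patients who are offered SBRT treatment, will accept the offer". In the other direction, "Cross-over from control arm to the SBRT treatment arm is extremely unlikely". With a one-sided 5% level and "a power of 80%, we require 49 patients per treatment arm", the section then adds the dropout allowance: "Finally, to allow for a 10% drop out rate, recruitment of 55 patients per group is intended".

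Data analysis sets the analysis by intention to treat. It defines dropout as death within three months or inability to supply pain scores and analgesic use, and says that for such patients "a worst-case analysis will be performed: dropped-out patients will be classified as non-responders". The comparison of response proportions is a χ2 test. The article gives no other rule for dropouts on the primary endpoint.

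The Discussion expects less dropout under this design: "We also expect lower drop-outs rates since patients in the control arm are not likely to withdraw from standard care".

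**The concern.** The two sections use different dropout models. Dividing 49 by 0.9 is the right allowance when dropouts are excluded: about 49 per arm remain and are compared at the planned rates. Under the rule in Data analysis nobody is excluded. Each dropout stays in the denominator as a failure, so both response rates are multiplied by one minus the dropout proportion and the difference shrinks by the same factor. The required sample size depends on the inverse square of that difference, so a single division by 0.9 is not enough.

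The stated power matters here because the article says SBRT will be adopted only if it is significantly better than usual care. A non-significant result therefore leads directly to non-adoption. If the power is about 72%, a real benefit of the assumed size is missed about 28% of the time, not 20%.

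**Working it through.** **Inputs** (Sample size considerations unless noted)
- Control response: 60%.
- Response after SBRT: 85%.
- Acceptance of the offer: 90%; those who refuse receive standard radiotherapy (Random selection). Cross-over from control is taken as zero.
- One-sided 5% level (z = 1.645) and 80% power (z = 0.842).
- Dropout 10%, recruitment 55 per arm.
- Dropouts scored as non-responders (Data analysis).

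**1. Reproduce the 49.** The intention-to-treat response in the offered arm is 0.9 × 85% + 0.1 × 60% = 82.5%. With p̄ the mean of the two rates and d their difference,

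n per arm = [1.645 √(2p̄(1−p̄)) + 0.842 √(p₁(1−p₁) + p₂(1−p₂))]² / d²

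For 0.60 vs 0.825: p̄ = 0.7125 and d = 0.225, so

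n = [1.645 √0.4097 + 0.842 √0.3844]² / 0.225² = 48.98, i.e. 49, the stated figure.

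**2. Reproduce the 55.** 49 / 0.9 = 54.4, rounded up to 55. If dropouts were excluded, 55 × 0.9 = 49.5 per arm would remain at 60% vs 82.5%, with power 80.4%. The inflation therefore fits an exclusion rule.

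**3. Apply the stated analysis rule.** With 10% of each arm scored as failures:
- control: 0.9 × 60% = 54.0%
- offered arm: 0.9 × 82.5% = 74.25%
- difference: 20.25 points instead of 22.5

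At 55 per arm the standard error is 0.0915 under the null (pooled) and 0.0894 under the alternative:

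power = Φ[(0.2025 − 1.645 × 0.0915) / 0.0894] = 72.0%

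Exact binomial enumeration of the uncorrected one-sided test gives 71.9%.

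**4. Sample size for 80% under this rule.** The formula in step 1 with 0.54 vs 0.7425 gives 68.3, so 69 per arm, with no further dropout inflation.

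**5. Sensitivity at 55 per arm**

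| Scenario | Rates compared | Power |
|---|---|---|
| 5% dropout in both arms | 57.0% vs 78.4% | 78% |
| 10% dropout in both arms (article's figure) | 54.0% vs 74.25% | 72% |
| 15% dropout in both arms | 51.0% vs 70.1% | 66% |
| 20% dropout in both arms | 48.0% vs 66.0% | 60% |
| 5% control, 10% SBRT (assumed, illustrative) | 57.0% vs 74.25% | 60% |
| 60% and 85% already count dropouts as failures | 60.0% vs 82.5% | 84% |

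**6. Another route to 49.** A two-sided 5% calculation for 60% vs 85%, ignoring refusal, also gives 49 (48.9). Under the stated dropout rule that design compares 54.0% with 76.5% and has 70.3% power at 55 per arm, so the shortfall does not depend on how the 49 was obtained.

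**The case against.** **The planning rates may already include dropouts.** The article does not say whether 60% and 85% are rates among evaluable patients; they come from cited studies that are not at hand. If those studies counted missing patients as failures, 55 per arm gives 84%. This stands as an alternative reading. However, a separate 10% allowance makes sense only if the rates refer to evaluable patients, and on the alternative reading the allowance is redundant. The text needs correcting either way.

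**Dropouts may be poor responders anyway.** Patients who die or become too ill to report might rarely have responded, so scoring them as failures would lose less. If the planning rates described all patients as though fully observed, and dropouts would have responded at half the arm average (an assumption), each rate falls by 5% and power is 78%; if none would have responded it is 84%. This does not apply when 60% and 85% are evaluable-patient rates: scoring 10% as failures then gives 54.0% and 74.25% whatever those patients would have done.

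**Worst-case may mean a sensitivity analysis.** The phrase allows that. But it is the only dropout rule given, it follows the intention-to-treat statement, and no completer analysis is named as primary.

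**The unequal-dropout scenario has thin support.** The Discussion speaks of withdrawal from care, not of death or missing pain data, and gives no percentages. That is fair: the 60% for this scenario is illustrative, and the conclusion does not rest on it.

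**The basis of the 49 is reconstructed.** The article attributes it to a difference of 15%, which does not match its own rates (60% vs 75% would need 120 per arm). That is a separate discrepancy; both routes that do give 49 lead to a shortfall here.

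**Conclusion.** The concern holds. The inflation from 49 to 55 and the scoring of dropouts as non-responders are incompatible, and the 80% power is wrong under the analysis the article describes. At the article's own 10% dropout, power at 55 per arm is about 72%, 8 points below the stated figure.

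The 72% rests on three things: 10% dropout in each arm, 60% and 85% as rates among evaluable patients, and an uncorrected one-sided 5% test. If the planning rates already count dropouts as failures, the error reverses and power is 84%. The validity of the test and its type I error are not affected; what is wrong is the stated chance of detecting the assumed benefit.

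**What to change.** Make Sample size considerations use the dropout rule in Data analysis, in one of two ways:

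- State that 60% and 85% are rates among evaluable patients, give the rates after 10% dropout (54.0% vs 74.25%, including 90% acceptance), and restate the power at 55 per arm as about 72% at one-sided 5%.
- Or, if the cited rates support it, state that 60% and 85% already count dropouts as non-responders, delete the inflation sentence, and give the power at 55 per arm as 84%.

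The cost is a short correction to one section and, in the first case, a less favourable power figure. Recruitment and conduct need not change. The correction does not raise the power, so a non-significant result should be read against the restated figure; 69 per arm is what 80% would have required.
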